# STUDY OBJECTIVES AND ENDPOINTS

## Primary objective

The primary objective of the study is to evaluate the safety and tolerability of ILB in patients diagnosed with ALS.

### Primary endpoint

- Frequency, seriousness and intensity of Treatment-emergent Adverse Events (TEAEs)
- Physical examination
- Vital signs
- Electrocardiogram (ECG) recordings
- Safety laboratory measurements: clinical chemistry, haematology including activated partial thromboplastin time (APTT)

## Secondary objectives

The secondary objective of the study is to evaluate efficacy of ILB in patients diagnosed with ALS.

### Secondary endpoints

- Functional rating with ALS Functional Rating Scale – Revised (ALSFRS-R)
- Functional rating with Norris scale
- Evaluation of ALS biomarker Neurofilament Light chain (NFL)
- Evaluation of biomarkers for neurological disorders (see 11.4.2)
- Pulmonary function (FVC)
- Quality of Life (QoL)
- Autonomous symptoms
- Levels of Hepatocyte Growth Factor (HGF)
- Pharmacokinetic measurements of ILB in plasma
- Changes in APTT (effect APTT)

## Exploratory objectives

To evaluate the effect of ILB on levels of *e.g.* growth factors, cytokines and biomarkers in plasma and cerebrospinal fluid (CSF).

# INVESTIGATIONAL PLAN

## Study design

This is a single-centre, open single-arm study where the safety, tolerability and efficacy of subcutaneously (s.c.) administered ILB will be evaluated in patients with Amyotrophic Lateral Sclerosis (ALS). There will be 10 visits to the clinic: 1 2-part screening visit (Visit 1a and Visit 1b), 5 IMP administration visits (Visit 2 to Visit 6) and 3 follow-up visits (Visit 7 to Visit 9). Each individual patient’s study participation will be approximately 4 months, including the screening and follow-up visits.

## Rationale for study design and dose

The design of the study is based on the aim to study safety, tolerability and efficacy of ILB solution in patients with ALS. Doses up to 24 mg/kg ILB has been administered to 79 healthy volunteers, but as ILB has never been administered to ALS patients and never more than two subsequent injections, a careful approach with low (1 mg/kg) and few doses (5 injections) with 1-week dosing interval has been chosen. The combined safety data from nonclinical and clinical studies indicate that the proposed dose can be administered without any safety concerns.

No control group is used as there are no spontaneous remissions or recovery of the disease. The progression of the disease is linear in the two clinical rating scales used, and therefore the rating of disease progression is reliable and standard in ALS research.

## Overall study procedures

Subjects will be screened for eligibility according to pre-defined criteria (see section 9.3 and 9.4) within 30 days prior to first administration of IMP (Visit 1a; day -30 to -7). If eligibility is confirmed at Visit 1a, the patients will return at Visit 1b (day -23 to -1) for collection of CSF and blood for analysis of NFL and other biomarkers of neurological disorders (see 11.4.2), and – if consented by patient – exploratory purposes (see 11.5). If it is found to be appropriate by patient or Investigator, the screening tests can be performed over several visits to avoid too strenuous strain on patient and next of kin.

Each subject will receive oral and written information about the study and the planned investigations and will have to give his or her signed and dated informed consent before any study-related procedures are initiated. On recruitment to the study, the patients will be evaluated for inclusion and exclusion criteria, and undergo a baseline assessment to include demographics, medical history, concomitant medication, vital signs, physical examination (including weight and height), ECG, haematology, and clinical chemistry. Patients will also complete a baseline assessment on the ALS Functional Rating Scale (ALSFRS-R), Norris rating scale and a quality of life assessment (Appendix 2-5). The patients will during 5 visits be administered ILB 1 mg/kg per week (Visit 2 to Visit 6), followed by 3 follow up visits (Visit 7 to Visit 9) over 10 weeks after the last dose. During the clinical trial, the patients will undergo regular assessments for safety and efficacy parameters.

The overall schedule of events for the study is presented in Table 2. For the visits with critical time points for study assessments, detailed schedule of events are presented in Table 3 (Visit 2 and Visit 6) and Table 4 (Visit 4). The procedures for all study assessments are described in detail in section 11.

Table 2 Schedule of events

| **Visit** | **1a** | **1b** | **2** | **3** | **4** | **5** | **6** | **7** | **8** | **9** |
| --- | --- | --- | --- | --- | --- | --- | --- | --- | --- | --- |
|  | Screening | Screening | Dosing^7^ | Dosing^7^ | Dosing^7^ | Dosing^7^ | Dosing^7^ | Follow-up | Follow-up | End of study  follow-up |
| **Day** | -30 to -7 | -23 to -1 | 1 | 8 | 15 | 22 | 29 | 36 | 50 | 99 |
| **Time window (days)** |  |  |  | ± 3 | ± 3 | ± 3 | ± 3 | ± 3 | ± 7 | ± 7 |
| Informed consent | X |  |  |  |  |  |  |  |  |  |
| Information on contraception | X |  |  |  |  |  |  |  |  |  |
| Information on medication | X |  |  |  |  |  |  |  |  |  |
| Eligibility criteria | X |  |  |  |  |  |  |  |  |  |
| Demographics | X |  |  |  |  |  |  |  |  |  |
| Medical history | X |  |  |  |  |  |  |  |  |  |
| Concomitant medications | X | X | X | X | X | X | X | X | X | X |
| Physical examination | X |  | X | X | X | X | X | X | X | X |
| Weight | X |  | X |  |  |  |  | X |  |  |
| Height | X |  |  |  |  |  |  |  |  |  |
| Vital signs | X |  | X | X | X | X | X | X | X | X |
| Forced vital capacity (FVC) | X |  | X | X | X | X | X | X | X | X |
| Haematology, including PK-INR | X |  | X | X | X | X | X | X | X | X |
| Clinical chemistry | X |  | X | X | X | X | X | X | X | X |
| Pregnancy^1^ | X |  | X | X | X | X | X | X | X | X |
| Drugs of abuse | X |  |  |  |  |  |  |  |  |  |
| Gamma-glutamyltransferase | X |  |  |  |  |  |  |  |  |  |
| HIV, hepatitis B and C | X |  |  |  |  |  |  |  |  |  |
| ECG | X |  |  |  |  |  |  | X |  |  |
| ALSFRS-R and Norris rating scales | X |  | X | X | X | X | X | X | X | X |
| Quality of life assessment | X |  | X |  | X |  | X |  | X |  |
| Autonomous symptoms | X |  | X | X | X | X | X | X | X | X |
| Biomarkers (CSF, plasma, serum) |  | X |  |  |  |  |  | X |  |  |
| ILB administration |  |  | X | X | X | X | X |  |  |  |
| Blood sampling PK, HGF, APTT^2^ |  |  | X^3^ |  |  |  | X^3^ |  |  |  |
| Blood sampling for explorative analyses |  | X |  |  | X^4^ |  |  | X |  |  |
| CSF sampling for exploratory analyses |  | X |  |  |  |  |  | X |  |  |
| Adverse events | X^5^ | X^5^ | X^5-6^ | X^6^ | X^6^ | X^6^ | X^6^ | X^6^ | X^6^ | X^6^ |

^1^ For women of child-bearing potential.

^2^ Effect APTT (not safety APTT).

^3^ For detailed time points and time windows on dose administration day, see Table 3.

^4^ For detailed time points and time windows on dose administration day, see Table 4.

^5^ Collection of baseline adverse events starts after the subject signs the ICF and continues until the first administration of ILB at Visit 2.

^6^ Treatment-emergent adverse events (TEAEs) are collected starting from first administration of the IMP (Visit 2) until the last visit (Visit 9).

^7^ IMP dosing/administration should occur within ±3 days from the specified day, with at least 4 days between two IMP administrations.

Table 3 Detailed schedule of events for Visit 2 and Visit 6

| **Visit 2 and Visit 6** |  |  |  |  |  |  |  |  |  |  |
| --- | --- | --- | --- | --- | --- | --- | --- | --- | --- | --- |
| Time points | Pre-dose^1^ | -15 min | 0 | 30 min | 1 h | 2 h | 2.5 h | 3 h | 4 h | 6 h |
| Time windows (min) |  | ± 5 |  | ± 5 | ± 5 | ± 5 | ± 5 | ± 5 | ± 5 | ± 5 |
| Concomitant medication | X |  |  |  |  |  |  |  |  |  |
| Physical examination | X |  |  |  |  |  |  |  |  |  |
| Weight | X^2^ |  |  |  |  |  |  |  |  |  |
| Vital signs | X |  |  |  |  |  |  |  |  |  |
| Forced vital capacity (FVC) | X |  |  |  |  |  |  |  |  |  |
| Haematology, incl PK-INR | X |  |  |  |  |  |  |  |  |  |
| Clinical chemistry | X |  |  |  |  |  |  |  |  |  |
| Pregnancy | X |  |  |  |  |  |  |  |  |  |
| ALSFRS-R and Norris | X |  |  |  |  |  |  |  |  |  |
| Quality of life | X |  |  |  |  |  |  |  |  |  |
| Autonomous symptoms | X |  |  |  |  |  |  |  |  |  |
| ILB administration |  |  | X |  |  |  |  |  |  |  |
| Blood sampling PK, HGF, APTT^3^ |  | X^4^ |  | X | X | X | X | X | X | X |
| Adverse Events / TEAEs | X^5^ | X | | | | | | | | |

^1^ Pre-dose (within 2 hours before administration of IMP).

^2^ Only at Visit 2. For calculation of IMP volume to be administered.

^3^ Time points are based on time from start of IMP administration. APTT for effect of IMP, not safety APTT. For details on blood sampling procedures, see Section 11.4.7.

^4^ Before injection of IMP, additional blood samples for sample dilution and generation of standard curves will be collected, see Section 11.4.6.

^5^ Treatment-emergent adverse events (TEAEs) assessment performed on Visit 6 only. Baseline events are collected on Visit 2.

Table 4 Detailed schedule of events for Visit 4

| **Visit 4** |  |  |  |  |  |  |  |  |  |  |
| --- | --- | --- | --- | --- | --- | --- | --- | --- | --- | --- |
| Time points | Pre-dose^1^ | -15 min | 0 | 30 min | 1 h | 2 h | 2.5 h | 3 h | 4 h | 6 h |
| Time windows (min) |  | ± 5 |  | ± 5 | ± 5 | ± 5 | ± 5 | ± 5 | ± 5 | ± 5 |
| Concomitant medication | X |  |  |  |  |  |  |  |  |  |
| Physical examination | X |  |  |  |  |  |  |  |  |  |
| Vital signs | X |  |  |  |  |  |  |  |  |  |
| Forced vital capacity (FVC) | X |  |  |  |  |  |  |  |  |  |
| Haematology, incl. PK-INR | X |  |  |  |  |  |  |  |  |  |
| Clinical chemistry | X |  |  |  |  |  |  |  |  |  |
| Pregnancy | X |  |  |  |  |  |  |  |  |  |
| ALSFRS-R and Norris | X |  |  |  |  |  |  |  |  |  |
| Quality of life | X |  |  |  |  |  |  |  |  |  |
| Autonomous symptoms | X |  |  |  |  |  |  |  |  |  |
| IMP administration |  |  | X |  |  |  |  |  |  |  |
| Blood sampling (exploratory)^2^ |  | X^3^ |  | X | X | X | X | X | X | X |
| TEAE | X | | | | | | | | | |

^1^ Pre-dose (within 2 hours before administration of IMP).

^2^ Blood samples collected for exploratory objective. Time points are based on time from start of IMP administration.

^3^ Before injection of IMP, additional blood samples for sample dilution and generation of standard curves will be collected, see Section 11.5

# STUDY POPULATION

## Screening log

Potential study subjects will be assessed for inclusion into the study at an initial screening visit. A screening number will be allocated to each patient. Investigators must keep a record of all screened subjects even if they were not subsequently included in the study. This information is necessary to verify that subjects were selected without bias. The reason for screen failure should be stated for all subjects screened but not included. The reason for withdrawal should be stated for all subjects included but not completed.

A patient may be rescreened. If a subject cannot receive the planned dose of IMP within 30 days after screening (*i.e.*, the time interval between signing informed consent until dose administration) the subject should be rescreened before proceeding in the trial. A result from CSF sampling at Visit 1b will be valid for 6 months.

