## Inclusion criteria

To be eligible for inclusion in the study, subjects must fulfil all the following criteria:

1. Willing and able to give written informed consent for participation in the study.
2. Clinical diagnosis of Amyotrophic Lateral Sclerosis (ALS).
3. Male or female patients between 18 to 80 years (inclusive).
4. Forced Vital Capacity (FVC) ≥ 65% of predicted value for gender, height and age at screening.
5. Evaluated with ALSFRS-R and Norris clinical rating scales for at least the past 4 weeks before study drug administration.

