## Exclusion criteria

Subjects must not enter the study if any of the following exclusion criteria are fulfilled:

1. Unable to understand information about the study or are expected not to collaborate with the study team.
2. Concurrent serious disease, other than ALS, at the discretion of the Investigator.
3. Pregnancy.
4. Patients of childbearing potential not willing to use adequate double contraception^[[1]](#footnote-2)^ with < 1% failure rate after the screening visit until the last visit.
5. Addiction to drugs or alcohol.
6. Confirmed HIV, hepatitis B or hepatitis C.
7. Known bleeding disorders or abnormal bleeding events.
8. Treatment with anticoagulant drugs warfarin and novel oral anticoagulants (NOAC) within the last 14 days prior to screening.
9. Treatment with Riluzole or Lamotrigine within the last 28 days prior to study drug administration.
10. Hypersensitivity to dextran sulfate.
11. Poor venous access.
12. Patients with clinically significant abnormal PK-INR, fibrinogen, von Willebrand factor and activated partial thromboplastin time (APTT) at screening.

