## Prior and concomitant therapy

Patients must not use anticoagulant drugs warfarin and novel oral anticoagulants (NOAC) during the study, and within the last 14 days prior to screening. Patients must not use Riluzole or Lamotrigine during the study, or within the last 28 days prior to study drug administration. Chronic intake of medication including herbal remedies and over the counter drugs on a stable dose for more than two months before screening is allowed. Hormonal contraception is allowed. If there is a need for use of other medication due to intercurrent disease at any time during the study period until end of study the decision will be declared by the patient to the investigator.

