### Biomarkers for neurological diseases, including NFL

Extent of presence of biomarkers for neurological diseases will be evaluated in serum, plasma and CSF sampled on Visit 1b and Visit 7.

The samples, apart from those for Compleasome analysis, will be transferred to Clinical Chemistry at SU before further transfer to Neurochemistry Laboratory Mölndal University Hospital for analysis. Samples for Compleasome analysis will be transferred to Department of Bacteriology at SU. Detailed procedures for sample handling will be provided in a separate lab manual.

The following biomarker parameters will be assessed:

| **In CSF** | **In serum** | **In plasma** |
| --- | --- | --- |
|  | Albumin | Neurofilament Light Chain (NFL) |
| Albumin | IgG | Compleasome |
| IgG | IgM |  |
| IgM |  |  |
| IgG index |  |  |
| IgM index |  |  |
| Tau |  |  |
| Phospho Tau |  |  |
| Neurofilament Light Chain (NFL) |  |  |
| Beta-amyloid |  |  |
| GFAP  Compleasome |  |  |

Any material remaining when the database is closed will be shipped to the Sponsor’s biobank and used for exploratory analyses (Section 11.5), if the patient has consented to this. Otherwise, samples remaining after database lock will be disposed of locally.

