## Total volume of blood and CSF per patient

The total volume of blood taken from each subject during the study is maximum 120 ml per visit and in total maximum 1080 ml during 4 months.

The total volume of CSF taken from each subject during the study is maximum 20 ml per visit (Visit 1b and 7), in total 40 ml.

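### The protocol lets a Visit 1b CSF sample stand for 6 months, so the only CSF biomarker baseline may be about 183 days old at first dose, against at most 23 days as scheduled

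*Protocol*

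**What the plan says.** Section 8.3 ties the baseline sample to the first dose: "If eligibility is confirmed at Visit 1a, the patients will return at Visit 1b (day -23 to -1) for collection of CSF and blood". Section 11.4.2 confirms that there are only two sampling occasions: "Extent of presence of biomarkers for neurological diseases will be evaluated in serum, plasma and CSF sampled on Visit 1b and Visit 7". Table 2 agrees. NFL is measured in both CSF and plasma, whereas tau, phospho-tau, beta-amyloid and GFAP are listed for CSF only.

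Section 9.1 sets a 30-day limit from consent to dosing. If it is missed, "the subject should be rescreened before proceeding in the trial". The next sentence is: "A result from CSF sampling at Visit 1b will be valid for 6 months". It mentions CSF only. It does not say whether the 6 months are judged at rescreening or at first dose.

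Section 16.6.2 summarises all biomarkers as changes from baseline and sets no limit on the age of the baseline. Section 16.7.4 includes the neurological biomarkers, NFL among them, in a possible interim analysis for futility and safety in 6-8 patients. Section 6.1 treats CSF NFL as the leading marker of disease activity. Section 8.2 explains that there is no control group.

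**The concern.** No inclusion or exclusion criterion uses CSF, and the sample is taken after eligibility has been confirmed. A CSF result that remains valid can therefore only be one that remains valid as the biomarker baseline. For a carried-over patient the rule replaces the 23-day maximum of section 8.3 with one of about half a year.

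The change to Visit 7 in such a patient would mix the effect of five ILB doses with months of untreated disease. No control arm exists to separate the two. The argument in section 8.2 that progression is linear concerns the two clinical rating scales, not the biomarkers. With 15 patients, and 6-8 at the interim, one such patient carries noticeable weight.

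**Working it through.** **Counting convention.** Section 8.3 puts Visit 1a at day -30 to -7 and describes this as within 30 days before the first dose. Day -30 is 30 days before Day 1 only if there is no Day 0, so that convention is used here. Day -23 is then 23 days before Day 1, and day -1 is 1 day before. Visit 7 (Day 36 ± 3) falls 32 to 38 days after Day 1, nominally 35.

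**As scheduled.**
- CSF age at first dose: 1 to 23 days.
- Visit 1b to Visit 7: 1 + 32 = 33 days, up to 23 + 38 = 61 days.
- Longest interval at nominal Visit 7: 23 + 35 = 58 days. Pre-treatment share: 23/58 = 40%.

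**With carry-over.** Assumption: 6 months is about 183 days (181-184 by calendar), counted from sampling to Day 1.
- CSF age at first dose: up to 183 days, and 183/23 = 8.0 times the scheduled maximum.
- Visit 1b to Visit 7: up to 183 + 38 = 221 days.
- At nominal Visit 7: 183 + 35 = 218 days. Pre-treatment share: 183/218 = 84%.
- If validity were instead judged at rescreening, with up to 30 more days to dosing, the age could reach 183 + 30 = 213 days. The text does not exclude this.

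**A short slip.** Suppose CSF is drawn 7 days after consent and the first dose falls on day 31 to 38 after consent. The sample is then 31 - 7 = 24 to 38 - 7 = 31 days old, at most 8 days beyond the scheduled maximum. The problem lies in long delays only.

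**Weight of one patient.** 1/15 = 7% of the trial; 1/8 = 13% to 1/6 = 17% of the interim. As an illustration, assume one patient at the ceiling and all others at 58 days. The mean interval at the interim rises from 58 to (7 × 58 + 218)/8 = 78 days with 8 patients, or (5 × 58 + 218)/6 = 85 days with 6.

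**Do the 28-day requirements cause it?** Exclusion criterion 9 reads "Treatment with Riluzole or Lamotrigine within the last 28 days prior to study drug administration", and inclusion criterion 5 reads "Evaluated with ALSFRS-R and Norris clinical rating scales for at least the past 4 weeks before study drug administration". Both count back from dosing, run in parallel and can be met wholly or partly before consent. A patient who starts either on the day of consent can be dosed on days 28, 29 or 30. A patient who stops the drug k days after consent has 3 - k permitted days, so none for k of 3 or more, and must be rescreened. The CSF need not be old even then. Take consent on day 0, drug stopped on day 5 and first dose on day 5 + 28 = 33. Visit 1a may be repeated up to day 33 - 7 = 26, and CSF may be drawn on days 33 - 23 = 10 to 33 - 1 = 32, inside the normal window. The clock forces a second screening here, not an old sample.

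**The case against.** Sparing a second lumbar puncture in ALS patients is a sound reason for the rule, although the protocol does not give it. It fits the concern in section 8.3 about strain on patients, and the CSF limit in section 11.6: "maximum 20 ml per visit (Visit 1b and 7), in total 40 ml". A full-volume repeat would bring the total to 3 × 20 = 60 ml. This stands, and the rule should be kept.

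The consequence is also limited. The primary objective is safety, the biomarkers are secondary and descriptive, and the interim is optional. Plasma NFL is not covered by the 6-month sentence. Subject listings would probably show the sampling date. The documents give no rate of change for CSF NFL, so the distortion can be stated in days but not in biomarker units. All of this stands, but it does not help the markers measured in CSF only. Presenting old baselines separately could be left to the SAP, which is not at hand. The validity period, its reference date and the plasma redraw, however, are matters of conduct that the protocol fixes.

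Two stronger readings are tempting. A reader might infer that the 28-day requirements make old baselines likely. The documents do not support that, because a patient delayed by them can still be sampled inside the window, and no rescreening rate is given. A reader might also infer that baselines will be taken on riluzole or lamotrigine. With the window and the 28-day rule both kept, CSF is drawn at least 28 - 23 = 5 days after the drug was stopped. Only a carried-over sample could differ, and the eligibility check before Visit 1b argues against such a draw.

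**Conclusion.** The point holds as a gap in the protocol with a cheap remedy. Section 9.1 permits a CSF baseline about 183 days old at first dose, roughly 8 times the scheduled maximum. Up to 84% of the baseline-to-Visit 7 interval would then precede treatment, against at most 40% as scheduled.

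This rests on 6 months being about 183 days counted to Day 1, on no Day 0, and on Visit 7 at its nominal day for the percentages. The 183 days are a ceiling, not an expected value, and reaching it needs a long delay after CSF sampling. The number of affected patients may be zero. A reader might infer a bias in favour of ILB, but the documents give no basis for a direction. The change is worth making because each affected patient would be 7% of the trial and 13-17% of the interim, and a proper baseline cannot be recovered after dosing.

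**What to change.** Keep the 6-month rule, and make these changes by amendment:

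- **Section 9.1:** state that the 6 months run from the CSF sampling date to the first dose, and that plasma NFL is redrawn at the rescreening Visit 1b.
- **Sections 16.6.2 and 16.7.4:** flag and list every patient whose baseline CSF was drawn more than 30 days before Day 1. Present the CSF change-from-baseline summary, and the CSF part of any interim, with and without those patients.

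Showing both versions is better than outright exclusion. Section 16.3 defines the full analysis set by dosing and at least one efficacy measurement, and section 16.7.2 says that the data present are used. Dropping dosed patients with data would sit badly with both in a trial of 15. The 30-day limit for consent to dosing and the Visit 1b window need no change.

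The cost is one amendment, one extra CSF summary, and perhaps one or two fewer patients in the restricted version. Rescreened patients give one more blood sample, within the volume limits of section 11.6. No repeat lumbar puncture is needed.

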## Number of subjects

15 patients will be included in the study. No formal sample size calculation has been performed for this study. The proposed sample size is considered sufficient in this early phase II development to provide adequate information on the patients.

